#### Interview Analysis

All phase I quantitative measures will be analyzed using percentages or means and SDs. These data will offer descriptive insights into each group of interviewees.

Interviews will be transcribed and checked by 2 research team members to identify any discrepancies before the analysis. Data from each type of participant will be analyzed separately using the following directed content analysis [69] approach. The analysis will begin with an a priori coding framework derived from BIT model constructs but will allow for the emergence of unanticipated codes. First, 2 team members will independently code the same transcript; the research team will convene to discuss identified codes to refine BIT codes and reach consensus regarding emergent codes. This process will be completed for each type of participant, resulting in a series of 3 codebooks. All transcripts will then be independently coded by 2 team members. The team will reconvene to discuss divergent codes with the goal of achieving 100% consensus; codes that remain discrepant following this discussion will be decided by a third, independent coder. Coding will occur on a rolling basis, to allow for periodic assessment of data saturation [70,71].

#### Building the TECH App

##### Anticipated Components

Although our final decision-making will be driven by phase I formative work, we anticipate including several theory-driven components in the TECH app. Specifically, in-app goal-setting and behavior tracking (eg, promoting self-efficacy) as well as delivery of accurate SU information (eg, helping to change attitudes and beliefs about SU) will leverage intrapersonal mechanisms of change. Interpersonal mechanisms of change will be targeted through a newsfeed for youth to post their progress (eg, modeling and social norms) and receive peer support (eg, social reinforcement). To protect against deviant peer influence [72], the app will be programmed to prevent negative (eg, *thumbs-down*) or covert (eg, direct messaging) features, and the moderator will monitor in-app activity daily.

##### App Development

The TECH app prototype will be built in partnership with Mooseworks Software LLC, a development company that builds apps from a software library of preprogrammed features, including, but not limited to, networking forums, community newsfeed, push notifications, tracking logs, and sharable posts. Guided by phase I formative work, the research team will engage in a series of meetings to select core elements and features of TECH in consultation with the software developer. Following the BIT model [55] (Figure 1), this process will match theory-driven intrapersonal (ie, self-efficacy, attitudes, and beliefs about SU) and interpersonal (ie, modeling, social norms, and social reinforcement) mechanisms of behavior change with CINI youth’s preferred app features. The research team will test the prototype’s functionality before launching phase II. In addition, the research team will populate the app with content solicited during phase I interviews with CINI youth to ensure the app is engaging to initial participants.

**Figure 1 figure1:**

Applying the behavior information technology model [55] to the proposed Teen Empowerment through Computerized Health app.

### Phase II: Beta Testing the TECH Prototype

#### Overview

In the next phase of the study, CINI youth (n=10) will beta test the TECH prototype. Beta testing enables users to identify and refine unclear components and troubleshoot software bugs. Methodologically, beta testing helps researchers reduce dissatisfaction, assess acceptability, and test and refine key study procedures (eg, app introduction, user safety agreement adherence, and metadata collection) before an RCT [73-76].

#### Beta-Testing Procedures

CINI youth recruitment, caregiver consent, and assent procedures will be identical to phase I, with one exception. Phase II will use a phased approach to recruitment, wherein the research team will wait to schedule baseline assessments until receiving consent-to-contact forms for 4 CINI youths. This will help ensure sufficient in-app peer presence for initial participants.

Enrolled CINI youth will attend a study session to complete baseline measures, the computerized ECTG program for cannabis use [56] and receive an introduction to the TECH prototype. A research team member will help participants download the app, create an anonymous account and log in, review the TECH app user safety agreement, and learn how to use each app feature. The research team member will help teenagers enter at least two cannabis-related behavior change goals derived from the ECTG program [56]. The TECH app introductions will be audio recorded to assess researcher adherence to the introduction protocols. The research team will monitor the TECH app activity daily to ensure prompt handling of any app functionality problems or participant concerns.

CINI youth will be asked to use the TECH app prototype for 1 month, completing a brief measure of acceptability each week. At the end of the beta-testing period, participants will complete a series of post–beta-testing measures of feasibility and acceptability. The TECH app metadata will be examined on an ongoing basis to monitor use patterns, note which app features are underused, and identify opportunities for targeted intervention to promote increased use. To test urine drug screen administration procedures for phase III’s pilot RCT, phase II CINI youth will be asked to complete a Clinical Laboratory Improvement Amendments–waived urine drug screen with eight panels (ie, cannabis, amphetamines, methylenedioxy-methylamphetamine, opiates, oxycodone, methamphetamines, cocaine, and benzodiazepines) during their post–beta-testing appointment. For in-person appointments, a research team member will request a urine sample and administer the dip test. Youth who complete appointments virtually will be mailed necessary screening materials before their appointment and receive step-by-step instructions to self-administer the dip test. Once the results are recorded, all the specimens and testing materials will be destroyed.

#### Beta-Testing Measures

##### Baseline

Measures will be identical to those used in phase II.

##### Feasibility

The feasibility of the TECH app prototype will be assessed using two primary indicators: (1) percentage of CINI youth willing to participate (recruited vs enrolled) with a target of 50% and (2) TECH usability, measured by automatically collected metadata. Available metadata will depend on design decisions following phase I formative work (eg, forum or newsfeed needed to make a post). Ideal app use would involve at least half of phase II participants using the app 2 or more times, spending an average of 30 seconds in the app when using it, posting at least once, and liking a peer’s content at least once.

##### Acceptability

We will measure the acceptability of the TECH app via four quantitative indicators: (1) percentage of CINI youth who withdraw from the beta-testing process, with a target of less than 20%; (2) weekly administration of the user version of the Mobile Application Rating Scale [77], an established, 20-item measure of an app’s engagement, functionality, esthetics, and information quality, with a targeted app quality mean score of 2.5, or higher (out of 5); (3) the Consumer Satisfaction Questionnaire [78], with a target of at least 70% of CINI youth indicating that they are satisfied and would recommend TECH to others; and (4) a structured, open-ended questionnaire to solicit feedback about the TECH prototype, including changes to content or features that could improve usability and engagement, administered at the end of the 1-month beta-testing period.

#### Beta-Testing Analysis

Due to the small sample size, phase II measures will only be used to offer insight into the feasibility of study procedures and guide the TECH app refinement. Data will be presented in aggregate and analyzed using means, SDs, or similar types of statistical analyses (eg, percentages).

#### Refining TECH

Similar to the development of the prototype, the TECH app refinement will follow the BIT model [55] and incorporate feedback provided by CINI youth during beta testing. The research team will work with our software developer to troubleshoot usability issues, consider modifications to address acceptability concerns, and finalize the TECH app.

### Phase III: Pilot RCT of the Final TECH App

#### Overview

In the final phase of the study, we will conduct a pilot RCT with CINI youth (n=60) to examine the feasibility, acceptability, and preliminary effectiveness of the TECH app. CINI youth recruitment, caregiver consent, assent, and baseline appointment procedures will be identical to those in phase II. Table 1 depicts the timing of phase III activities.

**Table 1 table1:** Schedule of enrollment, interventions, and assessments for phase III’s pilot randomized controlled trial.

		Enrollment, -t_1_	Allocation	Postallocation				Closeout, t_x_^a^
				t_1_^b^	t_2_^c^	t_3_^d^		
**Enrollment**								
	Screening	✓						
	Informed consent or assent	✓						
	User Safety Agreement	✓						
	Baseline	✓						
	Randomization		✓					
**Interventions**								
	TAU^e^ (all study participants)	✓						
	TECH^f^ app (only TAU+TECH participants)			✓	✓	✓		
**Phase III measures for all participants**								
	Demographics	✓						
	Child and Adolescent Services Assessment [64,65]	✓						
	Marijuana Use Questionnaire [66,67]	✓						
	Timeline Followback Interview [79-81]	✓		✓	✓	✓		
	Urine Drug Screens	✓		✓	✓	✓		
	Selected items on Global Appraisal of Individual Needs [82]	✓		✓	✓	✓		
	Selected items on cannabis use attitudes [83]	✓		✓	✓	✓		
	Marijuana Adolescent Problem Inventory [84]	✓		✓	✓	✓		
	Marijuana Effect Expectancy Questionnaire [85]	✓		✓	✓	✓		
	Cannabis Refusal Self-Efficacy Questionnaire [86,87]	✓		✓	✓	✓		
	Adapted Readiness to Change Questionnaire [88]	✓		✓	✓	✓		
	Descriptive, Injunctive, and Subjective Peer Norms [33]	✓		✓	✓	✓		
**Phase III measures completed by TAU+TECH participants**								
	Mobile Application Rating Scale (user version) [77]			✓	✓	✓		
	Adapted Consumer Satisfaction Questionnaire [78]			✓	✓	✓		
	Open-ended TECH app feedback questionnaire			✓	✓	✓		
**Other phase III measures not completed by participants**								
	Percent of CINI^g^ youth recruited vs enrolled						✓	
	Percent of CINI youth who withdraw from the study						✓	
	TECH app usability metadata						✓	

^a^Conclusion of study.

^b^1 month after baseline.

^c^3 months after baseline.

^d^6 months after baseline.

^e^TAU: treatment-as-usual.

^f^TECH: Teen Empowerment through Computerized Health.

^g^CINI: court-involved, nonincarcerated.

#### Pilot RCT Randomization

Upon completing the computerized ECTG program for cannabis use [56] at the baseline appointment, participants will immediately be randomized to 1 of the 2 treatment conditions. Participants will be randomized using an urn randomization spreadsheet [89], balancing for biological sex and frequency of cannabis use. Youth will be assigned at a ratio of 2 TAU+TECH to 1 TAU-only to ensure sufficient peer presence on the TECH app at any given time.

#### Pilot RCT Treatment Conditions

##### TAU-Only

The computerized ECTG program for cannabis use [56] and the family court’s standard care services will serve as the TAU-only condition in the pilot RCT.

##### TAU+TECH

Participants in the TAU+TECH arm will receive all TAU components and access to the TECH app. Immediately after randomization, a research team member will introduce participants to the TECH app using the same procedures used in phase II. TAU+TECH participants will be asked to use the TECH app for 6 months.

#### Pilot RCT Measures

Baseline, preliminary effectiveness, and putative mediator outcome measures will be administered to all phase III participants at all time points. Feasibility and acceptability measures specific to the TECH app will only be administered to participants randomized to TAU+TECH at the 1-, 3-, and 6-month follow-up appointments.

##### Baseline

All phase II baseline measures and phase III measures of preliminary effectiveness, secondary effectiveness, and putative mediators will be administered at baseline.

##### Preliminary Effectiveness Outcomes

These measures will be completed by all phase III participants at all assessments and will assess the preliminary effectiveness of TAU+TECH relative to TAU-only. The primary outcome measure will be CINI youths’ self-reported cannabis and other SU, as measured by the Timeline Followback Interview [79-81]. Youth will report their total days of cannabis and other SU, abstinence, high-volume use, co-use, and cannabis grams per day in the past 30 days. Youth self-reported SU will be corroborated by urine drug screens using the same procedures outlined in phase II unless adjustments are deemed necessary.

##### Secondary Effectiveness Outcomes

We will collect data on delinquent behavior to account for its bidirectional relationship with cannabis and other SU. Furthermore, 9 items adapted from the Global Appraisal of Individual Needs-Core [82] will assess past 30-day delinquency and legal system involvement.

##### Putative Mediators

We will collect six indicators of putative intrapersonal mechanisms of change: (1) attitudes toward cannabis use will be assessed by two items [83] that capture the perceived acceptability of personal cannabis use on a Likert scale, one positively framed (“Is it ok...?”) and one negatively framed (“How wrong is...?”); (2) the Marijuana Adolescent Problem Inventory [84], which includes 23 items on perceived cannabis-related consequences, rated on a 0-4 Likert scale; (3) The 6-item Marijuana Effect Expectancy Questionnaire-Brief [85], which gauges positive and negative expectations of cannabis use [90]; (4) the Cannabis Refusal Self-Efficacy Questionnaire [86,87], which uses 14 items measuring self-confidence to resist or refuse cannabis; (5) an adapted Readiness to Change Questionnaire [88], which will assess motivation to reduce cannabis use with 12-items; and (6) descriptive, injunctive, and subjective peer norms of cannabis use [33,68] as collected at baseline in prior phases.

##### Feasibility and Acceptability

These measures will be identical to those used in phase II; however, only CINI youth randomized to the TAU+TECH condition will be asked to complete measures regarding their experiences using the TECH app.

#### Pilot RCT Statistical Analysis

We will conduct preliminary analyses on key variables to examine distributional properties, identify outliers, and transform variables as needed. The conditions (ie, TAU-only vs TAU+TECH) will be compared on baseline demographic variables; differences will be controlled in subsequent analyses. Data analysis will follow intent-to-treat principles [91] and use multiple imputation methods [92] in the event of unplanned missing data. Due to the small sample size, we will be underpowered for significance testing. Instead, our goal is to obtain data on variable distributions, reliability, and effect size estimates for a future large-scale trial. For the same reason, we will not attempt to test for mediation but instead test associations with possible mediators. Findings will inform which variables to evaluate in a future trial.

We anticipate 80% retention [93] of phase III CINI youth (n=60), leaving 48 participants with complete data. This sample will be sufficient to determine the feasibility and acceptability outcomes. Primary preliminary effectiveness outcomes include cannabis and other SU. Putative mediators include intrapersonal and interpersonal mechanisms of change; delinquent behavior is the sole secondary outcome. Brief motivation-enhancing treatments produce short-term decreases in cannabis and SU [40,41], but technological adjuncts can help maintain reductions in SU for up to 6 months [94]. Thus, we expect CINI youth to report the highest rates of cannabis and other SU at baseline, with small to moderate decreases at 1 month that maintain at 6 months.

We will conduct a series of repeated measures analyses of covariance to predict outcomes by condition, test putative mediators, and control for baseline differences. We will also analyze dosage effects on each dependent variable and calculate partial eta squared (*η^2^*) to estimate proportions of variance associated with TECH. Despite effect size stability concerns in small samples [95], detection of small to moderate treatment effects on our primary outcomes alongside strong evidence of feasibility and acceptability could indicate preliminary efficacy of the TECH app as an adjunct to TAU. If such evidence is found, effect size estimates will be used to determine the sample size for a future, fully-powered RCT (eg, for power of 0.8, a small effect size [Cohen *d*=0.3] would require n=175 per group, whereas a medium effect size [Cohen *d*=0.5] would require n=64).

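### Covariate adjustment in the pilot RCT depends on observed baseline differences between arms, with no commitment to the urn factors or the baseline outcome, so precision and partial eta squared vary with the data

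*Protocol article*

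**What the plan says.** Pilot RCT Statistical Analysis gives the rule: "The conditions (ie, TAU-only vs TAU+TECH) will be compared on baseline demographic variables; differences will be controlled in subsequent analyses". Later in the same section the main model is a series of "repeated measures analyses of covariance to predict outcomes by condition, test putative mediators, and control for baseline differences". No fixed covariate list is given, and no test or threshold for deciding that the arms differ.

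Pilot RCT Randomization describes an urn scheme "balancing for biological sex and frequency of cannabis use", with 2:1 allocation: "Youth will be assigned at a ratio of 2 TAU+TECH to 1 TAU-only". The analysis section names neither balancing factor as a covariate.

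Table 1 and the Baseline paragraph under Pilot RCT Measures show that the outcome and mediator measures are taken at baseline. Sex is listed as a demographic under Interview Quantitative Measures; frequency of cannabis use is not.

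On purpose, the analysis section says the trial is underpowered for significance testing and that "our goal is to obtain data on variable distributions, reliability, and effect size estimates for a future large-scale trial". The effect measure is partial eta squared, used "to estimate proportions of variance associated with TECH".

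**The concern.** Both sentences make adjustment conditional on a difference seen in the data. Under sound randomisation, any such difference is chance. The rule therefore brings in whichever variable happens to be imbalanced, prognostic or not, and gives no assurance that the prognostic ones are used.

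This sits badly with the design. Sex and cannabis-use frequency mattered enough to be balanced by the urn. Sex is a demographic, so the rule reaches it only if the arms differ, which the urn makes less likely. Cannabis-use frequency is not a demographic, so the demographic rule does not reach it at all. The broader wording in the covariance sentence could reach it, but again only through a difference that the urn works against.

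The pilot's stated product is effect-size estimates. Adjusting for a strong baseline predictor narrows their intervals. Partial eta squared also changes with the covariates in the model, because they alter the residual variance in its denominator. If the covariate set is settled by the data, the value passed to the next trial has no fixed meaning.

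**Working it through.** **The plan's own figures.** The only power-based figures are for a future trial at power 0.8: 175 per group for d = 0.3 and 64 for d = 0.5. Assuming two-sided alpha 0.05 (not stated), n per group = 2(1.960 + 0.842)²/d², which gives 175 and 63. The t-based version gives 175.4 and 63.8. Both stated figures reproduce, and neither depends on this point.

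**Inputs from the article.** "We anticipate 80% retention [93] of phase III CINI youth (n=60), leaving 48 participants with complete data". At 2:1 this is 40 vs 20 randomised and 32 vs 16 complete.

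**Assumptions not in the article.** Baseline-outcome correlation r = 0.3, 0.5 or 0.7; normal outcome with a single follow-up; no missing data; sex effect 0.2 SD; five further demographics unrelated to outcome; selection at p < 0.05; a simple urn balancing sex and high/low baseline use.

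**Simulation.** 3,000 runs per setting, n = 48. The rule (demographics selected by observed difference, baseline use left out) is compared with prespecified adjustment for sex and baseline use. True difference 0.3 SD:

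| | r = 0.3 | r = 0.5 | r = 0.7 |
|---|---|---|---|
| Mean estimate, rule | 0.302 | 0.303 | 0.302 |
| Mean estimate, fixed | 0.302 | 0.304 | 0.303 |
| 95% half-width, rule (SD) | 0.625 | 0.630 | 0.628 |
| 95% half-width, fixed (SD) | 0.592 | 0.540 | 0.442 |
| Ratio of half-widths | 1.06 | 1.17 | 1.42 |
| Coverage, rule | 0.954 | 0.964 | 0.971 |
| Coverage, fixed | 0.948 | 0.953 | 0.953 |
| Mean partial eta squared, rule | 0.0388 | 0.0382 | 0.0367 |
| Mean partial eta squared, fixed | 0.0435 | 0.0479 | 0.0599 |

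**Cross-check on width.** In theory, omitting a baseline covariate widens the interval by 1/√(1 − r²), which is 1.05, 1.15 and 1.40. The simulated ratios are close to these.

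**Direction of the error.** With no true effect, mean estimates under the rule lie between −0.005 and 0.002. At r = 0.7 the rule's model standard error averages 0.311 against an empirical SD of 0.281, and the rejection rate is 0.029. At r = 0.3 the rejection rate is 0.044. The intervals are too wide, not too narrow.

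**Consequence for sizing the next trial.** With f² = η²/(1 − η²):
- r = 0.3: 0.0435/0.9565 = 0.0455 against 0.0388/0.9612 = 0.0404, ratio 1.13
- r = 0.5: 0.0479/0.9521 = 0.0503 against 0.0382/0.9618 = 0.0397, ratio 1.27
- r = 0.7: 0.0599/0.9401 = 0.0637 against 0.0367/0.9633 = 0.0381, ratio 1.67

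Required n scales roughly as 1/f², so the projected size moves by those factors. The absolute values are inflated at this sample size: with no effect at all, mean partial eta squared is already about 0.02 in both analyses. The comparison between analyses is the useful part.

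**What the rule would select.** If the comparison is a test at 0.05, at least one chance difference among k independent demographics has probability 1 − 0.95^k: 0.226 for k = 5 and 0.401 for k = 10. The simulation, with sex plus five demographics, gave 0.22 to 0.24. At 40 vs 20 such a test detects a 0.3 SD imbalance 19% of the time and a 0.5 SD imbalance 43% of the time.

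**The case against.** The strongest reply is that baseline use may well be in the model. The planned analysis is a repeated measures analysis of covariance, the phrase about controlling for baseline differences is not limited to demographics, and the outcomes are measured at baseline. A reader might infer that the rule drops baseline use. The article does not say so; it only fails to commit to including it. This stands, and it makes the width figures conditional. If baseline use is a covariate, the loss disappears. If baseline is instead one of the repeated levels, some loss can remain: a change from baseline to one follow-up has variance 2(1 − r) against 1 − r² for covariance adjustment (equal variances assumed), so the standard error ratio is √(2/(1 + r)), or 1.24, 1.15 and 1.08 at r = 0.3, 0.5 and 0.7.

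A reader might also infer that the effect estimates are wrong or that false positives increase. Neither follows: the estimate is unbiased and the intervals err on the wide side.

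Significance testing of baseline demographics is a further inference. The article says only that the arms are compared, so the selection probabilities and screening power above rest on an assumed 0.05 test. The urn also reduces imbalance rather than abolishing it, so sex can still enter.

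Finally, a condensed article may leave a covariate list to an analysis plan. That is fair, and a missing list is not the point. The article states a rule, and an analysis plan that follows it would inherit it. Even on the generous reading, adjustment remains triggered by observed differences.

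**Conclusion.** The point holds in a limited form, at moderate severity. The stated rule makes the covariate set depend on chance imbalance and does not commit to the urn factors or to the baseline value of each outcome. The treatment estimate remains unbiased.

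If baseline use is left out, intervals are about 6% to 42% wider than needed for r between 0.3 and 0.7, and conservative. That range rests on the simulation assumptions listed above, chiefly the correlation, which the article does not give. The shift in partial eta squared rests on the same assumptions. The general fact that the measure depends on the covariates entered does not.

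The documents do not support a stronger conclusion. They do not exclude baseline use, nothing points to bias or inflated error, and a 60-person pilot that disclaims significance testing and itself acknowledges unstable effect sizes is not invalidated by this rule. The reason to act is that the effect size is what the pilot hands on, and a better rule is available from data already planned.

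**What to change.** Delete the sentence that makes adjustment depend on baseline differences, and replace the matching phrase in the covariance sentence. Prespecify for each outcome model: arm, visit, biological sex, baseline frequency of cannabis use and the baseline value of that outcome. Where the outcome is itself days of cannabis use, the last two are nearly the same variable, so use a single baseline-use term. Report baseline demographics by arm descriptively. If a demographic is thought prognostic, name it now as a fixed covariate. State the covariate set beside every partial eta squared that is carried forward.

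The cost is wording only, as all these variables are already collected. Relative to a model that already carries the baseline outcome, it adds one degree of freedom (sex) or two (sex and baseline use frequency, with frequency entered as a single term). This is small against 48 completers.

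### The pilot's named effect size, partial eta squared, has no sign and is biased upward, so it is a poor basis for the efficacy signal and for sizing the next trial

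*Protocol article*

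**What the plan says.** All of the following is in the protocol article, Pilot RCT Statistical Analysis, unless noted.

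- The pilot is described as underpowered for significance testing. Its stated goal is to obtain distributions, reliability and effect size estimates for a larger trial.
- The model: "We will conduct a series of repeated measures analyses of covariance to predict outcomes by condition".
- Partial eta squared will be calculated "to estimate proportions of variance associated with TECH". It is the only effect-size statistic named for the pilot's own data.
- The reading of the result, prefaced by a caveat about effect size stability in small samples: "detection of small to moderate treatment effects on our primary outcomes alongside strong evidence of feasibility and acceptability could indicate preliminary efficacy".
- If such evidence is found, the effect size estimates will set the sample size of a fully powered trial. The illustration is that, "for power of 0.8", "a small effect size [Cohen *d*=0.3] would require n=175 per group", "whereas a medium effect size [Cohen *d*=0.5] would require n=64".
- Retention of 80% of 60 is expected, "leaving 48 participants with complete data". Analysis is by intention to treat with multiple imputation, so 60 may be analysed.
- Allocation is two TAU+TECH to one TAU-only (Pilot RCT Randomization). Hypothesis 2 is directional, predicting greater reductions with TAU+TECH (Study Aims and Hypotheses).

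**The concern.** Once significance testing is set aside, the size of the estimate carries the efficacy message. Partial eta squared suits that job badly, for two reasons.

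1. It is a ratio of sums of squares, so it cannot fall below zero. Chance differences between the arms push it up, and its average is above zero even when TECH has no effect. In a sample this small the upward push is about as large as a small effect.
2. It carries no direction. A rise in use under TECH and an equal fall give the same value. This is a live question for an app that connects justice-involved peers; the article describes design safeguards, introduced with the words "To protect against deviant peer influence" (Anticipated Components).

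Two things are at stake: a small effect could be announced when none exists, and the next trial could be planned on an inflated effect and so be too small.

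**Working it through.** **Inputs.** From the article: d=0.3 (small), d=0.5 (medium), power 0.8, 60 randomized, 80% retained, 2:1 allocation, follow-up at 1, 3 and 6 months. Assumed, because not given: two-sided alpha 0.05, one baseline covariate, and the correlations stated below.

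**The plan's own figures.** A two-sample t-test at two-sided alpha 0.05 and power 0.8 needs 175.4 per group for d=0.3 and 63.8 for d=0.5. The stated 175 and 64 reproduce. 60 × 0.8 = 48 also holds.

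**Mean of partial eta squared under no effect.** It follows a Beta(df1/2, df2/2) distribution, with mean df1/(df1+df2). For the arm effect with one covariate:
- 48 analysed: df2 = 48 − 3 = 45; mean 1/46 = 0.0217; median about 0.010.
- 60 analysed: df2 = 57; mean 1/58 = 0.0172; median about 0.008.

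**The plan's small effect on the same scale.** With p the share in one arm, f² = d²p(1−p) and eta² = f²/(1+f²).
- 2:1: f² = 0.09 × 2/9 = 0.020; eta² = 0.0196.
- 1:1: f² = 0.09 × 1/4 = 0.0225; eta² = 0.0220.

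On this simple conversion the null mean matches small with 48 analysed, and is 78% to 88% of it with 60 (0.0172/0.0220 and 0.0172/0.0196).

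**How the model changes the benchmark.** If d is on the single-visit raw SD, averaging visits and adjusting for baseline shrink the residual variance v, and f² = 0.020/v at 2:1. With all correlations assumed to be 0.5:
- One visit, baseline-adjusted: v = 1 − 0.25 = 0.75; eta² = 0.026.
- Three visits averaged, no baseline: v = (1 + 2×0.5)/3 = 0.667; eta² = 0.029.
- Three visits averaged, baseline-adjusted: v = 0.667 − 0.25 = 0.417; eta² = 0.046.

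**Chance that a null arm effect reaches small**, P(F(1, df2) ≥ df2 × f²), at 2:1:

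| Benchmark for d=0.3 | 48 analysed | 60 analysed |
|---|---|---|
| 0.0196, simple conversion | F ≥ 0.90: 35% | F ≥ 1.14: 29% |
| 0.026, one visit, baseline-adjusted | F ≥ 1.20: 28% | F ≥ 1.52: 22% |
| 0.029, visits averaged | F ≥ 1.35: 25% | F ≥ 1.71: 20% |
| 0.046, visits averaged, baseline-adjusted | F ≥ 2.16: 15% | F ≥ 2.74: 10% |

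The null distribution of the arm difference is symmetric, so half of each figure favours TAU-only. With correlations of 0.7 the last row falls to about 10% and 6%.

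**Sign and bias when there is an effect.** A simulation of 32 against 16 used one baseline covariate with correlation 0.5 and 20,000 runs. A true benefit and a true harm of d=0.3 both gave a mean partial eta squared of 0.047, against a true value of 0.026, and both reached 0.0196 in 59% of runs. Under no effect the bias-corrected version (epsilon squared) averaged about zero.

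**Consequence for sizing.** Required size is proportional to 1/f². If the mean estimate of 0.047 were taken at face value, f² would be 0.047/0.953 = 0.049 instead of 0.027. The next trial would be planned at 0.027/0.049, about 54% of the size needed.

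**The case against.** **Harm and benefit.** A reader might infer that the analysis could not tell harm from benefit. The article does not support that. The ANCOVA by condition yields arm means at each visit, which show direction, and Hypothesis 2 predicts greater reductions. An increase in use under TECH could not reasonably be presented as efficacy of an adjunct. The peer-influence passage is about app design and says nothing on analysis. The loss of sign belongs to the named statistic alone.

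**Null mean equal to small.** A reader might also infer that with no effect the estimate will typically come out small. The match in means holds only with 48 analysed and the simple conversion. The null median is about half the benchmark. With visits averaged and baseline adjusted, at assumed correlations of 0.5, small becomes about 0.046, twice the null mean. Nor does a between-arm d of 0.3 convert to a benchmark for the arm-by-visit interaction, so no exceedance chance is offered for that test.

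**Hedging.** The rule says could, claims only preliminary efficacy, admits low power and instability, and also requires strong feasibility and acceptability. That limits the harm. But feasibility and acceptability evidence on the app says little about whether a between-arm difference is real, and the stability caveat concerns imprecision, not upward bias or missing sign.

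**Reporting detail.** Intervals and adjusted differences are often left to an analysis plan, so their absence is not the point. The point is the statistic the article does name and the use it makes of effect sizes.

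**Sizing in d.** The sample size example is in Cohen d, so the next trial need not be sized from partial eta squared. If d is computed directly from the means, the sign is kept and this particular bias does not arise; if it is converted from partial eta squared, both problems carry over. The article does not say which.

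**Conclusion.** The concern holds in limited form and should be fixed, but it does not undermine the pilot. Partial eta squared is unsigned and biased upward, and with no effect its mean (0.022 with 48, 0.017 with 60) is of the same order as the plan's small effect. A null arm effect would reach small with a chance of roughly 10% to 35% per outcome, with about half of these favouring TAU-only. The upper end rests on the simple two-group conversion with 48 analysed. The lower end rests on averaging visits, baseline adjustment, assumed correlations of 0.5 and 60 analysed; stronger correlations would take it lower. The unsigned and biased nature of the statistic does not depend on these assumptions.

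**What to change.** - Make the effect size for the efficacy signal, and for sizing the next trial, the signed, covariate-adjusted between-arm difference in natural units (for example, days of use) and Hedges g, each with a 95% CI.
- Keep partial eta squared as a supplement at most.
- State that a point estimate in the small-to-moderate range is not by itself evidence of efficacy, and that any signal must favour TAU+TECH and be read with its interval.

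The cost is a few sentences and a different line of output from the same model. The possible claim becomes more modest: at 32 against 16, the unadjusted 95% interval for d is about ±1.96 × √(1/32 + 1/16) = ±0.60, which shows readers how little the pilot can say about effects of 0.3 to 0.5.
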